# Combining physical therapy and cognitive behavioral therapy techniques to improve balance confidence and community participation in people with unilateral transtibial amputation who use lower limb prostheses: a study protocol for a randomized sham-control clinical trial

**DOI:** 10.1186/s13063-019-3929-8

**Published:** 2019-12-30

**Keywords:** Amputee, Community integration, Activity, Fear avoidance, Virtual reality, Gaming

## Abstract

**Background:**

Low balance confidence is a prevalent yet overlooked issue among people who use lower limb prostheses (LLP) that can diminish community integration and quality of life. There is a critical need to develop rehabilitation programs that specifically target balance confidence in people who use LLP. Previous research has shown that multicomponent interventions including cognitive-behavioral therapy (CBT) techniques and exercise are feasible and effective for improving balance confidence in older adults.

Therefore, a cognitive behavioral–physical therapy (CBPT) intervention was developed to target balance confidence and increase community integration in people who use LLP.

**Methods/design:**

This randomized control trial will recruit 60 people who use LLP with low balance confidence. Participants will be randomized to the CBPT intervention condition or control condition.

**Discussion:**

The trial is designed to test the effects of the CBPT intervention on balance confidence and functional mobility in lower limb prosthesis users by examining self-reported and objective measures of community integration and quality of life. The trial will also examine the relationship between changes in balance confidence and changes in community integration following participation in CBPT intervention. Additionally, through participant feedback, researchers will identify opportunities to improve intervention efficacy.

**Trial registration:**

ClinicalTrials.gov, NCT03411148. Registration date: January 26, 2018.

## Background

Low balance confidence, defined as low self-perception in ones’ ability to maintain balance while performing specific activities, is a prevalent, yet overlooked issue among people who use lower limb prostheses (LLP). In a cohort of 435 community-dwelling individuals with lower limb amputation who had been living with LLP for at least 6 months, 65% reported levels of balance confidence below the threshold at which intervention is advocated for able-bodied adults [1, 2]. Low balance confidence can negatively impact community participation. In a cross-sectional study, low balance confidence was a significant predictor of social participation, even after accounting for mobility capability and other prosthesis-related characteristics [3]. Moreover, balance confidence at discharge from rehabilitation following a first amputation is a predictor of social participation 3 months after discharge [4], with low social participation significantly limiting quality of life [5, 6]. Low balance confidence is also associated with lower levels of physical activity [7].

Among people who use LLP, low balance confidence may be, in part, independent of functional ability; balance confidence and performance-based measures of balance are only moderately correlated [8] and, following discharge from rehabilitation, persons with a lower limb prosthesis continue to improve walking ability, while balance confidence does not continue to improve [4], suggesting the two may be independent. Accordingly, rehabilitation efforts that only target function may not necessarily improve balance confidence or increase community integration. In a 2014 study comparing two treadmill-based gait-training protocols for people who use LLP, participants demonstrated improved walking ability one month post-intervention (with no effect of intervention type) but reported no improvement in balance confidence [9]. Interventions that aim to improve community integration by alleviating restrictions due to low balance confidence may require multicomponent interventions that simultaneously address both physical ability and balance confidence.

A systematic review of 46 randomized control trials (RCTs) [10] and a separate meta-analysis of 24 RCTs [11] to improve balance confidence concluded that implementation of multicomponent interventions is feasible and effective in intact populations, particularly for persons with poor balance confidence. In most multicomponent interventions, physical abilities were addressed using physical therapy to target balance, gait, or strength; efficacy training (e.g., mastery experiences) increased the effects of physical therapy [11]. A major advantage of supplementing physical therapy exercises with cognitive behavioral therapy (CBT) strategies is that avoidance of activities can be directly targeted while addressing balance confidence. Previous interventions that have supplemented exercises with CBT demonstrated improvements in self-efficacy and increased activity up to 6 months post-intervention [11–13]. Supplementing exercises that specifically address balance ability with CBT strategies to address balance confidence may produce similar improvements in activity and self-efficacy in people who use LLP.

There is a critical need to develop and implement rehabilitation programs that specifically target balance confidence in order to increase community integration for people who use LLP. There are no current interventions to address balance confidence in this population. Therefore, we have developed a combined cognitive behavior and physical therapy (CBPT) intervention in which a behavioral therapist works in conjunction with a physical therapist to address underlying cognitions and physical skills that promote low balance confidence. Of particular note, the physical therapist will implement exercise in the intervention through the use of virtual reality (VR) games in the C-Mill Balance Suite (Motek; Netherlands). The games are displayed to the player on a 65-inch high-definition television screen at the front of the C-Mill, which is a 4 × 1 m (length × width) instrumented treadmill. Virtual reality games, in contrast to more traditional modalities, are used for several reasons. VR games provide a means to standardize progression based on performance and the ability to target multiple domains in few tasks while including a cognitive component, they can be adjusted for difficulty depending on the participants’ skill level, they encourage repetition of tasks and provide direct feedback in the form of a score, all of which promote motor learning [14, 15]. VR games are at least as effective as traditional physical therapy at improving balance and balance confidence in intact populations [16–18] and, moreover, are fun and motivating [14, 19, 20].

### Specific aims

#### Aim 1 (primary analyses)

Compare the effects of the combined cognitive behavior and physical therapy (CBPT) intervention condition versus a sham control condition on balance confidence and performance-based measures of balance and functional mobility in lower limb prosthesis users.
*Hypothesis 1a*: Participants receiving CBPT intervention will demonstrate improvements in balance confidence over time compared to participants in the control condition.*Hypothesis 1b*: Performance-based measures of balance will improve after CBPT intervention.*Hypothesis 1c*: Performance-based measures of functional ability will improve after CBPT.

#### Aim 2 (secondary analyses)

Compare the effects of CBPT intervention versus a sham control on self-reported and objective measures of community integration and on quality of life.
*Hypothesis 2a*: Participants receiving CBPT intervention will self-report and objectively demonstrate increased community integration over time compared to participants in the control condition.*Hypothesis 2b*: Participants receiving CBPT intervention will demonstrate improvements in quality of life compared to participants in the control condition.

#### Aim 3 (secondary analyses)

Examine the relationship between changes in balance confidence and changes in community integration following participation in CBPT intervention.
*Hypothesis 3*: For participants in the intervention condition, change in balance confidence from 0 to 25 weeks will be directly correlated with changes in community participation (0 to 25 weeks).

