**Fig. 1 Fig1:**
[figure not shown]
Flowchart of study participation

Participants in the intervention condition will complete eight weekly training sessions that include a virtual reality active gaming component (i.e., PT component), with CBT strategies that increase balance confidence by addressing subject-specific avoidance behaviors and maladaptive cognitions. Each session will last approximately 1.5 h. Participants in the control condition will complete a series of at-home upper-body seated exercises during this 8-week period after being taught by a physical therapist how to perform the exercises. The intention of the sham control is to blind participants to the study group. At the start of the study and at 8 (post-intervention), 16, and 24 weeks following group allocation, participants will complete survey-based outcome measures and activity monitoring. At baseline and post-intervention, participants will complete performance-based assessments of balance and of functional mobility. Outcomes measures are described below.

To minimize loss to dropout between baseline and final follow-up, research coordinators will routinely contact participants by telephone and email to maintain engagement in order to maximize participant adherence. Adherence will be quantified based on number of study visits attended and frequency of attendance. If a participant wishes to drop out of the study, they will be queried as to their reasons for doing so and every attempt will be made to address their concerns and to obtain the minimum amount of data necessary to address hypotheses related to the primary outcome (i.e., self-reported measures at 0 and 25 weeks).

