It is expected that 70 participants will be recruited in order to obtain a total of 60 eligible participants (30 intervention and 30 control participants), assuming a 15% drop-out rate. Using G*Power 3.1, a sensitivity analysis (with regard to Hypothesis 1a) was conducted, specifying a power of 0.80, an alpha of 0.05, and an average correlation of observations of 0.50. According to the analysis, with 30 participants in each group we will be able to detect a small to medium effect (f = 0.152) of intervention on ABC score over time with this design, which is consistent with the size of effect observed for older adults [10, 11]. We will have similar power for all hypotheses in Aim 2, which use the same analysis as Hypothesis 1a; we will have power to detect a medium effect size (d = 0.46) for Hypothesis 1b and a correlation of r ≥ 0.42 for Hypothesis 3.

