### Analysis plan

To test Hypothesis 1a we plan to use a 2 (group) × 4 (time point) mixed ANOVA to examine if there are significant differences in changes in ABC scores between the groups (i.e., an interaction effect), accounting for any missing data. In the event of a significant interaction, a post-hoc paired *t*-test will be used to compare ABC scale in the intervention group at 0 and 25 weeks and independent samples *t*-test to compare ABC scale between groups at 25 weeks.

To test Hypotheses 1b and 1c we will use a paired *t*-test to compare BBS scores and L-test times pre- and post-intervention. H1b and c do not compare time-related changes in performance between groups as they are only intended to assess the immediate effects of intervention.

The same analyses from Hypothesis 1a will be used to test all hypotheses in Aim 2. For Hypothesis 2a, a group × time interaction on self-reported community participation measures (CRIS, FAI, SF36 scales) and objective measures from the activity monitors will be tested. A false-discovery rate correction method will be used to minimize the likelihood of type I errors. For Hypothesis 2b, an interaction on the QoL score will be tested. In the event that H2a is not supported, alternative measures to assess integration will be considered.

To test Hypothesis 3 changes in ABC scores (0 weeks to 25 weeks) will be correlated with changes in self-reported and objective measures of community participation. A false-discovery rate correction method will be administered to minimize the likelihood of type I errors. In the unlikely event that Hypotheses 1a and 2a are not supported, this would not exclude the possibility of an association between subject-specific changes in confidence and participation. In such a case, a significant correlation would suggest that improving balance confidence can increase participation, but for optimum effectiveness of the intervention, one should only train individuals who are most likely to respond to the intervention (show large increase in ABC scores). As an initial step to identify commonality among “responders” we would employ a suite of supervised learning techniques (e.g., cluster and canonical correlation analysis) to explore multidimensional relationships among responses to individual items on the ABC, BBS, CRIS, and SF36.

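### Hypothesis 3 correlates changes in the CBPT arm only, yet the plan concludes from it that raising confidence raises participation; the control arm's slope should be reported beside it.

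*Protocol article*

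**What the plan says.** Aim 3 in the Protocol article is to "Examine the relationship between changes in balance confidence and changes in community integration following participation in CBPT intervention". Hypothesis 3 gives the population and the window: "For participants in the intervention condition, change in balance confidence from 0 to 25 weeks will be directly correlated" with change in participation over the same period. The Analysis plan gives the method: "changes in ABC scores (0 weeks to 25 weeks) will be correlated with changes in self-reported and objective measures of community participation", with a false-discovery-rate correction. It does not mention the control arm for this hypothesis.

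The same paragraph goes on to the case where Hypotheses 1a and 2a are not supported. There, a significant correlation is to be read as suggesting that better balance confidence can raise participation, and that only people likely to respond to the intervention should be trained.

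The data are wider than the analysis. Under Study design, at the start and "at 8 (post-intervention), 16, and 24 weeks following group allocation, participants will complete survey-based outcome measures and activity monitoring", with no exception for controls; Outcome measures repeats the schedule. The Participants section plans for "a total of 60 eligible participants (30 intervention and 30 control participants") and claims power for "a correlation of r ≥ 0.42 for Hypothesis 3".

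**The concern.** The analysis and the conclusion do not match. The analysis describes how two changes move together among people who all received CBPT. The conclusion concerns what improving confidence does, and whom to train.

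Joint movement can arise without CBPT. Participants are selected for an ABC score below 80, so some rise in ABC is expected on re-measurement in either arm. Several participation measures are self-reported, as ABC is, and may move with it for that reason alone.

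The gap matters most in the case for which the conclusion is written. If Hypotheses 1a and 2a fail, the trial has not shown that CBPT changes ABC or participation relative to control. Calling large ABC gains in the CBPT arm a response to CBPT then has no support from the randomised comparison. At stake are a statement about mechanism and a recommendation to restrict training to responders, both resting on an association with no reference.

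Secondarily, the test uses 30 of the 60 people who provide the measures.

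**Working it through.** **Inputs.** From the Participants section: 30 per arm, power 0.80, alpha 0.05 (sidedness not stated), detectable r of 0.42. I take 30 per arm as the number analysed and 25 weeks as the last visit.

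**1. The plan's own figure.** Noncentral-t model for a correlation: noncentrality = r√n / √(1 − r²), n − 2 degrees of freedom. With n = 30 and r = 0.42 this is 0.42 × 5.477 / 0.9075 = 2.535.
- One-sided, critical t 1.701: power 0.796, detectable r 0.422.
- Two-sided, critical t 2.048: power 0.687, detectable r 0.468.

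So 0.42 reproduces with n = 30 and a one-sided test. This confirms that Hypothesis 3 is powered on one arm.

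**2. One arm against both arms, two-sided.** Fisher z with k covariates: detectable r = tanh[(1.960 + 0.842) / √(n − 3 − k)].
- n = 30, k = 0: 2.802 / √27 = 0.539, so r = 0.492.
- n = 60, k = 1 (arm): 2.802 / √56 = 0.374, so r = 0.358.

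| Method (two-sided) | n = 30 | n = 60 with arm term |
|---|---|---|
| Fisher z | 0.492 | 0.358 |
| Exact distribution of r | 0.485 | 0.355 |
| Noncentral t | 0.468 | 0.348 |

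Exact power at r = 0.42 is 66% with n = 30 and 92% with n = 60 and an arm term. One-sided, the detectable r is 0.42 to 0.445 with n = 30 and about 0.31 to 0.32 with n = 60.

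The false-discovery correction raises these limits. The outcome section lists nine participation measures (three from the monitors, two CRIS scales, three SF36 subscales, one FAI score). At the strictest step, 0.05 / 9 two-sided, the detectable r is about 0.60 with n = 30 and 0.44 with n = 60.

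**3. When pooling helps.** The n = 60 figures assume the same slope in both arms. Let the control slope be a fraction f of the CBPT slope, with equal variances. The pooled slope is then (1 + f)/2 of the CBPT slope, and its standard error is 1/√2 of the one-arm standard error. The test statistic changes by the ratio [(1 + f)/2] × √2 = (1 + f)/√2. This equals 1 at f = √2 − 1 = 0.41.

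Simulation with 30 per arm, two-sided 5%, CBPT r = 0.42 and equal residual variance (control slopes and variances are assumptions):

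| Control slope / CBPT slope | Power, pooled slope | Power, CBPT arm only |
|---|---|---|
| 1 | 92% | 66% |
| 1, control ABC-change variance halved | 84% | 66% |
| 0.5 | 72% | 66% |
| 0.4 | 66% | 66% |
| 0.25 | 56% | 66% |
| 0 | about 40% | 66% |

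**4. Precision of the slope difference.** In the same simulation with equal variances, the difference between arms is detected with about 40% power if the control slope is zero and about 14% if it is half the CBPT slope.

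**The case against.** The restriction to the CBPT arm is deliberate. Aim 3 and Hypothesis 3 both ask about people who took part in CBPT, and a secondary within-arm correlation with a stated population and window is a legitimate analysis. The sham was chosen because it should not promote balance confidence during weight-bearing, and CBPT works directly on avoidance, so the slopes may well differ. Section 3 of the working shows that pooling could then cost power. This stands, and it is why the CBPT-arm test should remain.

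Three stronger readings are tempting, and the documents support none of them.
- A reader might infer that the plan cannot detect moderate associations. Two-sided power at r = 0.42 is about 66%, and on the apparent one-sided basis it is about 80%.
- A reader might infer that using only the first and last visits is an error. Change to the last visit is a defensible choice. The gain from weeks 8 and 16 depends on an error structure that is not given, and the FAI looks back 3 to 6 months, so its week-8 score largely covers time before the intervention.
- A reader might infer that the protocol claims an association specific to CBPT. Hypothesis 3 makes no such claim.

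The objection does not answer the mismatch of inference. The Analysis plan leaves the within-arm question when it writes of what improving confidence can do, and it does so for the case where the randomised comparisons have failed.

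**Conclusion.** The point holds as a mismatch between a one-arm correlation and the conclusion attached to it. It does not show that the Hypothesis 3 test is wrong. Without the control slope, the planned correlation cannot be told apart from joint change that would have occurred without CBPT.

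The loss of information is real but conditional. The two-sided detectable correlation falls from about 0.47–0.49 to about 0.36 if the slopes and the ABC-change variances are similar in the two arms. The pooled slope has no advantage once the control slope is at or below about 40% of the CBPT slope. Replacing Hypothesis 3 with a pooled slope is therefore not supported. Adding the control-arm estimate is a cheap improvement to a secondary aim.

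**What to change.** Keep the CBPT-arm association as the Hypothesis 3 test. Pre-specify one supporting model in all randomised participants for each participation measure: change in participation on change in ABC, arm, and the arm-by-change interaction. Report with confidence intervals the CBPT slope, the control slope and their difference, and the arm-adjusted pooled slope from the same model without the interaction.

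Reword the conclusion in the Analysis plan so that it depends on these estimates:
- If the control slope is similar, describe a general association between the two changes, not a response to CBPT, and do not use it to support selecting responders.
- If the CBPT slope is clearly steeper, a link tied to CBPT becomes more plausible, though it remains an association within arms.
- If the interval for the difference is wide, say that the question is unresolved.

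State in the Participants section whether the 0.42 is one- or two-sided and that it refers to 30 people. Reconcile the 25-week label with the 24-week visit. Use of weeks 8 and 16 is optional.

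The cost is analysis wording only, with no new data or visits. The downside is that the slope difference will be imprecise with 30 per arm, so it should be presented as an estimate and a non-significant difference should not be read as equality.

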#### Aim 4 (exploratory analyses)

Identify opportunities to improve intervention efficacy. This exploratory aim involves key informant interviews to identify themes related to residual barriers to social activity and mobility, the CBPT strategies that were deemed most effective, and additional strategies to address social participation and mobility barriers (e.g., behavioral activation, different physical therapy strategies).

## Methods/design

### Study design

Sixty people who use LLP with low balance confidence will be randomized to the CBPT intervention condition or control condition (Fig. 1). Participants will be assigned to one of two randomization plans based on etymology of amputation: vascular causes (e.g., diabetes, peripheral vascular disease) or non-vascular causes (e.g., trauma, osteomylistis). For each plan, a block randomization will be used with a block size of 4 to ensure balance among the exercise groups throughout the study. The randomization plan will be developed by a researcher uninvolved with the project using www.randomization.com and sealed envelopes will be used to conceal the randomization schedule until enrolled participants are assigned to a group. For scheduling purposes, to ensure that the necessary clinicians are on site at the time that group assignment is revealed to the participant (at visit occurring ~ 1 week following enrollment), envelopes will be opened after the participant leaves the university after completing the enrollment visit.

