### Participants

Participants will be veterans recruited directly from local VA Medical Centers or civilians/veterans recruited from the community. Recruitment at local VA hospital centers will take place through a two-step process. In step 1, medical records will be reviewed for persons having a unilateral transtibial amputation and prescribed prosthesis at least 6 months prior. Veterans found through medical record search will be sent a form letter indicating they may qualify for a study and should respond to the letter only if interested in additional information. The letter will ask them to complete and return a copy of the Activities-specific Balance Confidence (ABC) scale. In step 2, participants with ABC scores less than 80% will be called by research coordinators to determine eligibility through the use of an IRB-approved script. Recruitment of civilians/veterans from the community will primarily take place through flyers posted at local prosthetic clinics, support groups, and physical therapy offices.

All participants must meet the following criteria: at least 18 years of age, unilateral transtibial amputation, at least 6 months experience with using a definitive prosthesis, an ABC score less than 80. Participants will be excluded for open wounds on weight-bearing surfaces, inability to stand unassisted and weight-shift for 2.5 min (i.e., inability to perform the CBPT intervention), ill-fitting or ill-functioning prosthesis as determined during a screening with the study prosthetist, prohibited by primary care physician or research physician to engage in mild exercise, history of neurodegenerative diseases and stroke, or currently receiving physical therapy. No other concomitant therapies or interventions are excluded from the study and all other standards of care are permitted. Screening and all other study-related activities will occur only after the participant provides written informed consent, which will be taken by a study team member.

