### Study administration

This trial will not include a coordinating center nor a Trial Steering Committee and there is no Stakeholder and Public Involvement Group involved. The study PI will undertake all administrative oversight, aside from that provided by the local IRB. He will have regular meetings with all investigators to discuss problems as they arise as well as progress of the study. The study PI will work with a study coordinator to identify potential recruits and consent will take place by any of the listed investigators on the study.

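### A single published block size of 4 in both strata makes up to about a third of allocations deducible in advance by anyone who can follow earlier assignments; undisclosed, varying block lengths would remove most of that certainty cheaply

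*Protocol article*

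**What the plan says.** All references are to the protocol article.

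- **Strata (Study design).** "Participants will be assigned to one of two randomization plans based on etymology of amputation": vascular or non-vascular.
- **Blocks (Study design).** In each plan, "a block randomization will be used with a block size of 4 to ensure balance among the exercise groups throughout the study". No other block size is mentioned. Allocation is 1:1 (Participants: "30 intervention and 30 control participants").
- **Concealment (Study design).** A researcher outside the project makes the list, and "sealed envelopes will be used to conceal the randomization schedule until enrolled participants are assigned to a group".
- **Timing (Study design).** Each envelope is opened once the participant has left the enrollment visit. The stated reason is scheduling: "to ensure that the necessary clinicians are on site at the time that group assignment is revealed to the participant".
- **Who recruits.** Research coordinators check eligibility by telephone for those who answer the VA letter (Participants). A coordinator helps the PI identify recruits, and "consent will take place by any of the listed investigators on the study" (Study administration). The research coordinator also manages appointments and schedules (Discussion).
- **Who is blinded.** The article names the participants (Study design), the assessors of the Berg Balance Scale and L-test (Functional abilities) and the person who links GPS and step data (Activity monitoring). It names nobody who recruits, screens or takes consent.

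**The concern.** With one known block length, a tally of past assignments within a stratum shows when an arm's two places in the block are used up, and the rest of that block is then certain. Sealed envelopes hide the next card, but they do not stop a forecast made from cards already opened.

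The tally is plausible to keep. The block size is printed in an article published during recruitment, the stratum follows from the cause of amputation, and the arms look quite different to staff: eight laboratory sessions against seated exercises at home. The coordinator role appears on both sides, in eligibility calls and in scheduling.

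Foreknowledge matters only where someone can act on it. At least one entry criterion is a judgement by study staff: "ill-fitting or ill-functioning prosthesis as determined during a screening with the study prosthetist". The timing of a call or visit is also flexible. The trial has 60 participants and a self-reported primary outcome, so selective entry by expected motivation or response could shift the comparison.

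**Working it through.** The article gives no figure for predictability, so there is none to reproduce. Its power statement is not affected by this point.

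**Inputs.** Block size 4, two strata and 60 randomized (Study design); 1:1 allocation, hence 2 + 2 per block, and about 70 recruited (Participants). The split between strata is not given, so every split was counted.

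**Step 1: certainty within a block of 4.** There are 6 equally likely orderings of 2 + 2. An allocation is certain once one arm has used both its places.

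| Position | 1 | 2 | 3 | 4 |
|---|---|---|---|---|
| Probability already certain | 0 | 0 | 1/3 | 1 |
| Probability best guess is right | 1/2 | 2/3 | 2/3 | 1 |

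Certain: (0 + 0 + 1/3 + 1) / 4 = (4/3) / 4 = 33.3%.
Best guess right: (1/2 + 2/3 + 2/3 + 1) / 4 = (17/6) / 4 = 70.8%, against 50% by chance.

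**Step 2: this trial, with incomplete last blocks.**

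- 30/30 split: each stratum has 7 full blocks and 2 left over. Certain: 2 × 7 × 4/3 = 18.7 of 60 = 31.1%. Best guess: 7 × 17/6 + 1/2 + 2/3 = 21.0 of 30 = 70.0%.
- 20/40 split: 5 + 10 = 15 full blocks. Certain: 15 × 4/3 = 20.0 of 60 = 33.3%.
- Over all splits of 60: 18.7 to 20.0 (31.1% to 33.3%). If 70 were randomized: 22.0 to 22.7 (31.4% to 32.4%).

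**Step 3: varying block lengths.** These were simulated at 30 per stratum (4,000 runs), with a predictor who knows the set of lengths and the full history but not each draw. The length sets are illustrative assumptions.

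| Block lengths | Certain | Best guess right | Gain over chance |
|---|---|---|---|
| Fixed 4 | 31.2% | 70.0% | 20.0 points |
| 4 and 6 | 5.7% | 68.8% | 18.8 points |
| 4, 6 and 8 | 2.2% | 67.5% | 17.5 points |

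The simulated 31.2% for fixed blocks agrees with the exact 31.1%.

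**Step 4: how much can still be changed.** Recruitment began on April 5, 2018 and was planned to end on December 31, 2020, a span of 1,001 days (Trial status). The article appeared on December 30, 2019, day 634, so 634 / 1,001 = 63% of the window had passed. Assuming even accrual, 60 × 0.367 = about 22 participants remained, of whom about 22 × 1/3 = 7 would have had a certain allocation under fixed blocks.

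**The case against.** A reader might infer that unblinded recruiters run the randomization and will know a third of the assignments. The article does not support that. It puts the opening of envelopes in the passive and does not say who does it, who was told the block size during recruitment, or who can see past assignments by stratum. It condenses a fuller manual in which such roles may be set out. Other institutions take part and several people may take consent, so no single recruiter need hold a complete tally. This stands: exposure of recruiting staff is an inference from overlapping coordinator roles and from the absence of any stated blinding for them.

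The room for discretion is also limited. The main entry criterion is an ABC score below 80, standing and weight-shifting is a timed ability, and exercise may be prohibited by the participant's own physician. Prosthesis fit remains a study judgement, as does the timing of contact. Baseline ABC is one of the time points in the primary analysis, which partly handles selection on the starting score, though not selection on unmeasured prognosis.

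The remedy has limits too. A recruiter acting on a best guess keeps 18.8/20.0 = 94% or 17.5/20.0 = 88% of the advantage over chance, and it comes too late for those already randomized. Small blocks also serve a stated purpose, balance throughout a small two-stratum trial. All of this stands. It lowers the weight of the point, but it does not touch the count of certain allocations or the low cost of reducing it.

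**Conclusion.** The point holds as a conditional risk in a rule that the article states. A fixed block of 4 in two strata leaves up to 31% to 33% of allocations (18.7 to 20.0 of 60) deducible with certainty. That ceiling requires someone who knows the block size, the candidate's stratum and all earlier allocations in that stratum; to cause bias, that person must also be able to influence entry. The article describes no separation that would prevent this, and it does not establish that anyone is in that position.

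Nothing here shows that selection bias occurred, and the block size is neither miscalculated nor contradicted elsewhere. Varying the block length is a worthwhile, inexpensive improvement that removes most of the certainty but little of the overall guessability. Its benefit is confined to participants still to be randomized: on even accrual from the publication date, about 22 people and about 7 certain allocations.

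**What to change.** For envelopes not yet used, have the uninvolved researcher regenerate each stratum's list, beginning after the current block is complete. Draw block lengths at random, for example from 4 and 6, or from 4, 6 and 8. Do not disclose the new lengths to anyone who recruits, screens or takes consent until enrolment ends. Submit the change to the IRB, as Setting and ethics approval requires for protocol modifications.

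The cost is two regenerated lists, new envelopes and an IRB modification. The largest possible imbalance within a stratum at any time rises from 2 to 3 (blocks up to 6) or 4 (blocks up to 8). If the switch is made before the current block is finished, that stratum also carries one partly completed block.
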